### Adverse event monitoring and reporting

Adverse events will be carefully monitored during this study. The team at the clinical intervention sites will monitor and report all minor and serious adverse events that occur, if any, from enrolment to the end of the study. The following adverse events could occur will be (effects of tDCS and risk of fall during gait):

During the stimulation: certain effects may be perceived such as : (1) a sensation of pruritus under the active electrode during the first 2 min of switching on the current, (2) in rare cases, headache during stimulation, (3) prickling sensations and (4) a sensation of fatigue.

After stimulation: headaches, nausea and nocturnal insomnia following the stimulation.

## Discussion

### Impact

Comparison of the effects of anodal and placebo tDCS on the different motor functions should demonstrate that anodal tDCS significantly improves gait and balance in chronic stroke by reducing the variability of the COM during gait, static and static-dynamic balance tasks. This study should demonstrate that anodal tDCS improves kinematic and kinetic gait parameters, and performance on functional tests, and reduces the clinical symptoms of stroke (reduced spasticity and increased strength). We will also determine: (1) if the changes induced by anodal tDCS are correlated with the patient’s level of function according to the clinical evaluation scales and (2) if there is a relationship between functional performance and improvements following anodal tDCS and the time since lesion. Moreover, comparison of the effects of tDCS over time will allow the kinetics of action of the stimulation to be determined. Furthermore, since each task is evaluated by several different methods, the comparison of the effects of anodal tDCS on the task carried out during the stimulation with a similar task not tested during the stimulation will determine if the effects of tDCS on a motor task are potentialised by the practice of a task during stimulation as suggested by Bikson et al. (2013) [47]. However, if the results show that tDCS has no effect on the variables analysed, the comprehensive data collection will allow analysis of whether the lack of effects depends on the profiles or the level of performance of the patients. If no robust explanation is found, this would suggest that anodal tDCS has no effect on gait and balance. In this case, further studies should investigate other stimulation conditions (bilateral stimulation, stimulation of another cortical zone of or repeated stimulations sessions). The analysis of the different Val66Met profiles could also provide explanations regarding a lack of effect.

Although has been shown that tDCS can improve some motor activities in patients with chronic stroke [55–57], there is much variation between studies as well as across subjects [58, 59]. The present study should provide some answers regarding this variability by investigating the influence of the patients’ profiles and whether changes in cortical excitability are able to induce changes in patients’ gait. It has recently been shown that the combination of tDCS and robot-assisted gait training (RAGT) on a treadmill positively improved gait performance in patients with chronic stroke compared to the RAGT only [60], but not in patients with subacute stroke [61]. Andrade et al. (2017) showed that 10 sessions of tDCS can reduce the risk of falls in patients with chronic stroke [62]. Despite these positive results, many questions remain unanswered [63]. The results of the present study will constitute a useful base to determine the aspects of function that tDCS improves the most in patients with hemiparesis, and is an essential first phase towards the validation of this technique as a treatment in patients, coupled with task-oriented training (Additional file 1).

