### Statistical analysis

The details of calculation of the COM and the COP are available in the ‘Appendix’ section.

The sample size was calculated from the data by Bonnyaud et al. (2016) [24]. Bonnyaud et al. [24] studied the raw trajectory length of patients with hemiparesis compared to a group of healthy subjects during a gait task (Timed Up and Go Test), which is very similar to what we will do by evaluating the variability of the COM during gait. Based on the data of Bonnyaud et al. [24], there was a difference of 99.5 cm in the trajectory lengths of the patients with stroke and the healthy subjects. In the present study, we hope to find a reduction in this difference following anodal tDCS; however, following placebo tDCS, there should be no difference. To determine the size of the sample of patients, we used the standard deviations of the patients with hemiparesis included in the study by Bonnyaud et al. [24].

In order to obtain a 50 to 60% reduction of the difference in COM variability between anodal and placebo tDCS with a power of 90% and a moderate to large effect size, a sample of 39 subjects is necessary. We therefore decided to include 40 patients in order to cover any drop outs. All the calculations were carried out using XLSTAT 2016® with a threshold of 90% power and a significance of *α* = 0.05.

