#### Analysis of outcome measures

Patient characteristics (age, gender, etc.) will be described by means, medians and standard deviations for continuous numeric parameters and by frequency tables with 95% confidence intervals for qualitative parameters.

A chi-squared test with Yates’ correction or the Fisher’s exact chi-squared test will be used to compare the distributions of qualitative variables.

There will be two possibilities for quantitative and ordinal variables:If the data are close to a normal distribution, means will be compared using Student’s *t* test

Comparison of the means or medians will be carried out for all the functional clinical data and the data determined following the movement analyses during the different evaluations. Repeated measures analysis of variance (ANOVA) and/or analysis of covariance as well as *t* tests (and/or non-parametric sign tests), corrected using the Scheffé adjustment, will be used for multiple comparisons.2.If the variables do not follow a normal distribution or if the small number of subjects studied does not allow the normality to be determined, we will use non-parametric tests such as Wilcoxon for the comparison of two variables, or Kruskall-Wallis for the comparison of more than two variables

All tests will be carried out with a bilateral threshold of first order of 5%.

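### A null result in a trial of 39 to 40 patients sized for a moderate-to-large effect cannot support the stated reading that anodal tDCS has no effect on gait and balance

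*Protocol article*

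**What the plan says.** The *Impact* section of the Discussion considers the case in which the results show no effect on the variables analysed. The data would then permit "analysis of whether the lack of effects depends on the profiles or the level of performance of the patients". The next sentence draws the conclusion: "If no robust explanation is found, this would suggest that anodal tDCS has no effect on gait and balance". The section goes on to call for studies of other stimulation conditions, and closes: "The analysis of the different Val66Met profiles could also provide explanations regarding a lack of effect".

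The sizing is under *Statistical analysis*. The target is introduced with "In order to obtain a 50 to 60% reduction of the difference in COM variability between anodal and placebo tDCS", and the result is given as "with a power of 90% and a moderate to large effect size, a sample of 39 subjects is necessary"; 40 patients are to be included. No SD, numeric effect size or named test is printed. *Analysis of outcome measures* plans tests of difference only: "All tests will be carried out with a bilateral threshold of first order of 5" per cent. The article ties no equivalence margin, smallest relevant effect or confidence-interval criterion to the null reading.

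**The concern.** A test of difference that fails to reject does not show that the difference is zero. What a null result can exclude depends on the width of the confidence interval, and a trial sized for a moderate-to-large effect leaves smaller effects open. The article bridges the gap with a second step: look for a patient-profile explanation and, if there is none, lean towards no effect. That step carries little information if the trial can detect only large differences between profiles.

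The article presents the trial as an essential first phase towards validating the technique. An unsupported statement of no effect could turn later work to other montages, sites or repeated sessions, when the proper reading might be that this one was tested with too little precision. The trial was ongoing at submission, so the reading can be settled before reporting.

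**Working it through.** **Inputs.** Two-sided α = 0.05 (*Analysis of outcome measures*); power 90% and N = 39, with 40 included (*Statistical analysis*); a two-period cross-over in which each patient receives both conditions, so the comparison is paired (*Study design*). Effects are in units of the SD of the paired anodal-minus-placebo difference. The paired t test is my assumption.

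**1. The plan's own figure.** N = 39 cannot be reproduced strictly, because the effect size is given only in words. Solving backwards for the effect that gives 90% power at n = 39:
- two-sided paired t (noncentral t, 38 df): 0.533
- two-sided normal approximation, (1.960 + 1.282)/√39: 0.519
- one-sided paired t: 0.477

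So the design effect is about 0.53 SD, range 0.48 to 0.53. Taking moderate to large as the conventional 0.5 to 0.8, the two-sided paired t test needs 44 down to 19 patients, so 39 sits at the moderate end.

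**2. Precision.** The 95% half-width is t(0.975, 38)/√39 = 2.024/6.245 = 0.324 SD (0.320 with 40 patients). This depends only on n. Against the back-solved design effect it is 0.324/0.533 = 61%. An observed difference of exactly zero still leaves ±0.32 SD open. A result just short of significance has an interval reaching 2 × 0.324 = 0.65 SD, beyond the design effect itself.

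**3. Power for smaller effects, one outcome, two-sided paired t.**

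| True effect (SD of paired difference) | n = 39 | n = 40 |
|---|---|---|
| 0.2 | 23% | 24% |
| 0.3 | 45% | 46% |
| 0.4 | 68% | 69% |
| 0.5 | 86% | 87% |

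At half the design effect (0.533/2 = 0.27 SD), power at n = 39 is 37%.

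**4. What a positive claim of absence would need.** For two one-sided tests at 5%, 90% power and a true difference of zero, n = ((1.645 + 1.645)/margin)². A margin of 0.3 SD gives 121 patients; 0.2 SD gives 271.

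**5. The search for an explanation.** For a two-group split, the smallest interaction detectable at 80% power is about (1.96 + 0.84) × √(1/n₁ + 1/n₂). The splits are assumed, since the article gives no frequencies:
- 20% (8 v 31): 2.8 × 0.397 = 1.11 SD
- 30% (12 v 27): 2.8 × 0.347 = 0.97 SD
- 40% (16 v 23): 2.8 × 0.326 = 0.91 SD

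These are roughly twice the design effect. The plan speaks of correlation with profile, so a split is a simplification, and it takes the SD of the difference as equal in both groups.

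I have not converted these figures to centimetres. The planning figure, "there was a difference of 99.5 cm in the trajectory lengths of the patients with stroke and the healthy subjects", is a trajectory length in a Timed Up and Go task, whereas the primary outcomes are the variability of centre-of-mass and centre-of-pressure displacement.

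**The case against.** The strongest reply is that this is one hedged sentence in a Discussion, outside the statistical section, and that it binds no analysis. It says only that the result would suggest no effect, and the call for other stimulation conditions partly confines the reading to this single-session montage. Rules for reading a null result are often left to a full protocol or analysis plan, neither of which is shown. All of this lowers the weight. It does not remove the point, which concerns an inference the article itself states, not a detail it leaves out.

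Three stronger readings are tempting and are not supported.

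- A reader might infer that the profile search is post hoc, prompted by a null result. The article lists correlation with the patient's profile as its third secondary objective, gives it a subsection under the outcomes, and repeats it unconditionally in *Impact* just before the null scenario. Only the Val66Met analysis is described solely in connection with a lack of effect. Even there, sampling is planned at the inclusion visit with a reason given, and genotype is not part of the condition that leads to the no-effect sentence.
- A reader might turn 45% power at 0.3 SD into a 55% rate of false no-effect statements. The sentence requires no effect across several variables and also no robust explanation. The single-test miss rate is therefore an upper bound on that rate.
- A reader might treat 0.53 SD as the sponsor's planned effect. It is back-solved under an assumed test and cannot serve as a fixed threshold.

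**Conclusion.** The point holds for the inference itself: absence of a detected effect, even together with absence of a profile explanation, would not be evidence that anodal tDCS does nothing for gait and balance. At most, a null result could count against an effect of the planned size, and only where the confidence interval excludes it.

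The half-width of 0.32 SD and the powers of 23% and 45% at 0.2 and 0.3 SD rest on about 39 completers and a paired t analysis of one outcome. The comparison with the design effect also rests on the back-solved 0.48 to 0.53 SD. The interaction figures rest on an assumed 20 to 40% split. The conclusion is not sensitive to the exact design effect, because a trial with 90% power at its target has low power at half that target. The hedge and the Discussion setting make this a modest correction, but one worth making before results are reported.

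**What to change.** Replace the sentence in *Impact* with a reading rule:

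- Report the anodal-minus-placebo difference with its 95% confidence interval for each primary outcome.
- If the test is non-significant, state only whether the interval excludes the effect used for sizing. The sponsor should print that value, with the SD it rests on.
- If the interval does not exclude it, call the result inconclusive for this single-session montage.
- Make no statement that the technique has no effect.

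The profile analyses are already planned whatever the main result. Put the Val66Met analysis on the same footing and label it exploratory.

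The cost is a change of wording plus intervals from analyses already planned, with no extra patients or measurements. The downside is a more cautious negative conclusion.

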### Trial status

The trial is ongoing at the time of manuscript submission.

## Appendix

### Centre of mass (COM) displacement

Displacement of the COM during gait, the trajectory tracking and the balance tasks will be calculated using the following equation:

$$ CO{M}_x\kern0.5em =\kern0.5em \frac{m_1{x}_1+{m}_2{x}_2+\cdots {m}_i{x}_i}{M}\kern0.5em =\kern0.5em \frac{1}{M}{\sum}_{i=1}^N{m}_i{x}_i $$

where

*M* = whole body mass

*m*
_*i*_ = mass of the ith segment = (whole body mass) × (mass fraction for ith segment from the anthropometrics data)

*x*
_*i*_ = the x-coordinate of the centre of mass for the ith segment with respect to the calibration origin

*N* = the number of body segments

### Centre of pressure (COP) displacement

Displacement of the *COP*
_*x*_ and *COP*
_*y*_ during the balance tasks will be calculated using the following equation:

$$ CO{P}_x\kern0.5em =\kern0.5em \frac{M_y+{F}_x\ast {z}_{\mathrm{o}}}{F_Z} CO{P}_y\kern0.5em =\kern0.5em \frac{M_x+{F}_y\ast {z}_{\mathrm{o}}}{F_Z} $$

where

*F*
_*x*_ = is the resultant of the forces on the x-axis

*F*
_*y*_ = is the resultant of the forces on the y-axis

*F*
_*z*_ = is the resultant of the forces on the z-axis

*M*
_*x*_ = is the moment of force on the x-axis

*M*
_*y*_ = is the moment of force on the y-axis

z_o_ = origin of the platform (the distance is given by the manufacturer)

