### Primary outcomes

#### Before, during, immediately after, and 30 min after tDCS cessation

Variability of the COM

As previously indicated, the variability of COM displacement is a strong marker of dynamic stability during locomotion and it is altered in patients with stroke.

The primary outcome measure of this study is thus the assessment of the variability of the displacement of the COM during gait and during trajectory tracking over the ground, evaluated by 3D gait analysis and the variability of the displacement of the COP during a static-balance task on a force platform. It will be recorded once during the inclusion visit then four times during the stimulation visits: before, during, immediately after and 30 min after cessation of stimulation. A reduction in the variability of COM displacement should result in an improvement of spatiotemporal, kinematic and kinetic gait parameters.

The 3D gait analysis will be conducted with a 3D optoelectronic system (Motion Analysis Corporation, Santa Rosa, CA, USA, sampling frequency 100 Hz) with eight optoelectronic cameras. Thirty markers will be placed on the patient’s body (following the Helen Hayes model commonly used by the biomechanical community for gait analysis [53]). The relative displacement of each segment will be calculated from these coordinates (flexion/extension, abduction/adduction, internal/external rotation). The marker trajectories will then be filtered using a fourth-order zero-lag Butterworth low-pass-filter, with a 6-Hz cut-off frequency [54]. The data from two force platforms combined with the kinematic and anthropometric data will be used to evaluate the displacement of the COP and COM during gait and balance tasks.Instrumented gait task

Ten trials of gait at a comfortable speed and 10 trials at maximal speed will be recordedInstrumented balance task

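### The appendix's two centre-of-pressure equations carry the same sign pattern, so for any non-zero platform offset one axis, not identifiable from the text, is computed wrongly

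*Protocol article*

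**What the plan says.** The Statistical analysis section sends the reader to the Appendix for the COM and COP calculations. Under Centre of pressure (COP) displacement, the Appendix says that both coordinates "during the balance tasks will be calculated using the following equation" and prints:

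- COP_x = (M_y + F_x·z_o)/F_z
- COP_y = (M_x + F_y·z_o)/F_z

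The same z_o serves both lines and is described as the "origin of the platform (the distance is given by the manufacturer". No value or sign is given for it, and no axis directions or handedness are stated.

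Under Primary outcomes, the COP part of the primary outcome is "the variability of the displacement of the COP during a static-balance task on a force platform". The same section lists initiation of the first step among the balance conditions and analyses the COP trajectory there as well.

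**The concern.** The x and y components of a cross product are antisymmetric. If the moment and the shear correction have the same sign on one axis, they must have opposite signs on the other. The printed pair has a plus on both. This is a stated rule, not a detail left to another document, and if coded as printed it gives a wrong coordinate on one axis.

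Two different faults could follow. One is mirroring of an axis, which swaps left and right or front and back but leaves variability unchanged. The other is a spurious term proportional to horizontal force, which mixes shear into what should be a position. A change in push-off between anodal and placebo sessions could then appear as a change in COP trajectory.

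**Working it through.** **Inputs.** The two equations and the single z_o come from the Appendix. The article gives no platform offset or forces, so every size below rests on assumed values, shown as ranges.

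**Derivation.** For a force F applied at (x, y, z), M = r × F gives

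- M_x = y·F_z − z·F_y, so y = (M_x + z·F_y)/F_z
- M_y = z·F_x − x·F_z, so x = (−M_y + z·F_x)/F_z

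Substituting into the printed pair:

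- If z_o = z: COP_y = y (right), and COP_x = −x + 2·z·F_x/F_z (mirrored, plus a shear term).
- If z_o = −z: COP_x = −x (mirrored only), and COP_y = y − 2·z·F_y/F_z (wrong).

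Either way, the size of the error on the faulty axis, beyond mirroring, is 2·z_o·F_h/F_z.

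**Numerical example (assumed values).** Take r = (30, −50, −40) mm and F = (20, −12, 700) N. Then M_x = −35 − 0.48 = −35.48 N·m and M_y = −0.8 − 21 = −21.8 N·m.

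- z_o = −40 mm: COP_x = (−21.8 − 0.8)/700 = −32.3 mm; COP_y = (−35.48 + 0.48)/700 = −50.0 mm.
- z_o = +40 mm: COP_x = (−21.8 + 0.8)/700 = −30.0 mm; COP_y = (−35.48 − 0.48)/700 = −51.4 mm.

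The true point is (30, −50) mm. Neither sign of z_o recovers both coordinates, even allowing for mirroring.

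**Could an unstated convention rescue the pair?** All 64 combinations were tried: direction of each of the three axes, right- or left-hand moment rule, action or reaction force, and sign of z_o. With non-zero z_o, none makes both equations exact and none makes both right up to mirroring. In all 64, exactly one axis is right up to mirroring. With z_o = 0, none of the 32 remaining combinations is exact on both axes, but all 32 are right up to mirroring.

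**Size of the error, 2·z_o·F_h/F_z in mm, with F_z = 700 N assumed:**

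| z_o | F_h = 1 N | 5 N | 50 N | 100 N |
|---|---|---|---|---|
| 20 mm | 0.06 | 0.29 | 2.86 | 5.71 |
| 40 mm | 0.11 | 0.57 | 5.71 | 11.43 |
| 55 mm | 0.16 | 0.79 | 7.86 | 15.71 |

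The first two force columns stand for quiet standing and the last two for step initiation.

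**Effect on static variability.** In a simulated quiet-standing example (z_o 45 mm, shear SD 3 N, shear independent of COP), the SD of COP_x was 6.06 mm as printed against 6.04 mm true, a difference of 0.02/6.04 = 0.3%. The correlation with the true value was −0.998. The error term itself had an SD of 0.38 mm. If shear were instead correlated with COP, the SD in this example could move by at most that amount: 0.38/6.04 = 6.3%.

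**The case against.** The best defence accepts the algebra and disputes the consequence. Most of it stands.

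- **Primary outcome.** A reader might infer that the primary COP measure is compromised. The documents do not support that. The measure is variability in a static task, mirroring leaves variability unchanged, and the shear term is sub-millimetre in quiet standing under every assumed input. The same formula also applies to both sessions of a within-patient cross-over, so mirroring cannot favour either condition.
- **Which axis.** A reader might conclude that COP_x is the faulty line. That holds only if z_o is the signed surface coordinate. With the opposite sign, COP_y is at fault.
- **Side reversal.** Mirroring would exchange sides or front and back, but the outcome sections name no COP side-asymmetry endpoint. The shift towards the non-hemiparetic limb appears only in the Background.
- **Obstacle crossing.** It uses a COP trajectory too, but it is a secondary outcome and the Appendix ties the equations to the balance tasks. Extending the fault there is inference.
- **What was actually run.** Platform software may compute the COP correctly, and a minus sign may have been lost in typesetting. Neither can be shown or excluded from the text.

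Two defences do not succeed. Setting z_o to zero leaves only mirroring, but the Appendix includes z_o explicitly as a distance supplied by the manufacturer. Defining M_x and M_y with different handedness would reconcile the pair, but that is not a single axis convention and is not stated. Nor is this ordinary condensation in an article: the formula was printed, and as printed it is inconsistent.

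**Conclusion.** The printed pair is wrong as written. For non-zero z_o, exactly one axis carries an error of 2·z_o·F_h/F_z beyond mirroring, under any single axis convention. The text does not settle which axis. This conclusion rests only on statics and the two printed lines.

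The sizes rest on assumed values (z_o 20–55 mm, F_z 700 N). They are about 0.06–0.8 mm in quiet standing, where the effect on static COP variability is probably negligible, and about 3–16 mm in step initiation, where the COP trajectory could be distorted. The sample-size statement that "a sample of 39 subjects is necessary" does not use these equations and is unaffected. The documents do not show that any trial data were processed with the printed form.

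**What to change.** - Replace the pair with a consistent one. With z_o as the signed coordinate of the surface, this is COP_x = (−M_y + F_x·z_o)/F_z and COP_y = (M_x + F_y·z_o)/F_z. The platform manufacturer's own matched pair would serve equally well.
- State the axis directions and the sign of z_o beside the equations.
- Check the processing code against a known load at a known point, including a horizontal force. With a purely vertical weight F_h = 0, so the shear term vanishes and only mirroring would show.
- Reprocess stored force data only if the printed form turns out to have been used.

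The cost is a sign, a sentence and a short bench test. No new patient measurements are needed if the raw force data have been kept. The article reports the trial as ongoing at submission, so the check could be made before analysis.
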